### Data analysis

#### Statistics

Interval scaled variates will be summarized with means and standard deviations (SD) or medians and interquartile ranges where appropriate. Dichotomous variates will be described as ratios and percentages.

#### Univariate analysis

T-tests will be used to compare means between groups and chi-squared tests to compare dichotomous variables.

#### Multivariate analysis

To adjust for unequal distribution of parameters at baseline, multivariate regression models, linear models in case of an interval scaled outcome and logistic regression in case of a dichotomous outcome will be performed.

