### Study population and recruitment

According to the inclusion and exclusion criteria (Table 1), we will investigate patients planned for transurethral resection of the prostate presenting with UTIs (defined as ≥10^4^ colony forming units/mL and symptoms such as urgency, frequency, and/or dysuria). The following variables will be considered: age, type of bladder emptying, prostate size, urinalysis, bladder and pain diary, IPSS questionnaire.

**Table 1 Tab1:** Study inclusion and exclusion criteria

Inclusion criteria	Exclusion criteria
• Age > 18 years • Urine culture (taken by mid-stream urine; or from the existing transurethral or suprapubic catheter): ≥10^4^ colony forming units/mL of predefined uropathogens (i.e. Enterococcus spp., *Escherichia coli*, Proteus mirabilis, Pseudomonas aeruginosa, Staphylococcus spp., and Streptococcus spp.) • Uropathogens sensitive to Pyo bacteriophage • Symptoms: Urgency, frequency, and/or dysuria • Written informed consent	• Fever >38 °C • CRP >100 mg/L • Acute prostatitis • Concomitant fungal urinary tract infection • Current antibiotic treatment or antibiotic treatment within the last 7 days (exceptions: subjects with an active catheter associated urinary tract infection who have received prior antibiotics may be enrolled provided a minimum of 48 h has elapsed between the last dose of the prior antibiotic and the time of obtaining the baseline urine specimen. Subjects receiving current antibiotic prophylaxis for catheter associated urinary tract infection who present signs and symptoms consistent with an active new catheter associated infection may be enrolled provided all other eligibility criteria are met including obtaining a pre-treatment qualifying baseline urine culture) • Any rapidly progressing disease or immediately life-threatening illness including but not limited to: acute hepatic failure, respiratory failure, and septic shock • No informed consent

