### Study outcome measures

Primary: Success of intravesical treatment, defined as normalization of urine culture (no evidence of bacteria, i.e. <10^4^ colony forming units/mL) after 7 days of bacteriophage, placebo, or antibiotic treatment.

Secondary: Adverse events, in categorization according to the National Cancer Institute Common Terminology Criteria for Adverse Events (CTCAE) version 4 in grade 1 to 5 (http://ctep.cancer.gov/protocolDevelopment/electronic_applications/ctc.htm) during treatment phase.

Tertiary: a) Changes in bladder and pain diary assessment of number of voids, number of leakages, post void residual, pain assessment using a visual analog scale (0 (no pain) to 10 (strongest possible pain)), b) IPSS items at baseline versus day 7 under intravesical bacteriophage, placebo, or antibiotic treatment.

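### Baseline adjustment is justified by chance imbalance, and the plan does not commit to adjusting the tertiary diary, pain and IPSS outcomes for their own baseline values

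*Protocol article*

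**What the plan says.** Under Univariate analysis, the article states: "T-tests will be used to compare means between groups and chi-squared tests to compare dichotomous variables". Under Multivariate analysis it adds regression, for one stated purpose: "To adjust for unequal distribution of parameters at baseline, multivariate regression models". The sentence ends: "linear models in case of an interval scaled outcome and logistic regression in case of a dichotomous outcome will be performed".

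The tertiary outcomes, under Study outcome measures, include "Changes in bladder and pain diary assessment of number of voids, number of leakages, post void residual", a pain score, and "IPSS items at baseline versus day 7 under intravesical bacteriophage, placebo, or antibiotic treatment". Study design and Investigations both show that the diary and IPSS are completed before treatment and again at its end, so each patient who completes both assessments has a baseline and a day-7 value.

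Study population and recruitment lists baseline variables: "The following variables will be considered: age, type of bladder emptying, prostate size, urinalysis, bladder and pain diary, IPSS questionnaire". It does not call them model covariates.

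The primary endpoint is dealt with separately. Determination of sample size assigns both main hypotheses to a continuity-corrected chi-squared or Fisher's exact test.

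**The concern.** Randomisation makes any baseline difference between arms a chance event. A covariate is worth including because it predicts the outcome, and it can be named before any data are seen. How unequally a parameter is distributed can be known only afterwards. A model built on that rationale therefore depends on which differences happened to arise in this sample, and a strongly prognostic variable that happens to be balanced would have no stated reason to be included.

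For the diary, pain and IPSS outcomes, the obvious prognostic variable is the same measure at baseline. The plan collects it but does not commit to using it as a covariate. With 27 patients per arm, the loss of precision could matter for these outcomes.

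**Working it through.** **The plan's own figure.** For superiority the article assumes success rates of 0.2 and 0.6, power 0.8 and type I error 0.05, and gives 27 per arm. The two-sided normal formula gives 23 per arm without and 28 with continuity correction. Exact two-sided Fisher power at 27 per arm is 80.2%. The stated size is therefore reproduced. It concerns the unadjusted primary test, and nothing below alters it.

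**Inputs for the tertiary outcomes.** n = 27 per arm, from the article. The baseline/day-7 correlation r is not in the document, so 0.3, 0.5 and 0.7 are assumed. The standard deviation is taken as equal at both times and set to 1.

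**Formulas.** The variance of the between-arm difference is 2/n times:
- t-test on day-7 values: 1
- t-test on change: 2(1 − r)
- ANCOVA: 1 − r²

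ANCOVA relative to the change score is (1 − r²) / [2(1 − r)] = (1 + r)/2.

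| r | ANCOVA, 1 − r² | Change, 2(1 − r) | ANCOVA/change, (1 + r)/2 |
|---|---|---|---|
| 0.3 | 0.91 | 1.4 | 0.65 |
| 0.5 | 0.75 | 1.0 | 0.75 |
| 0.7 | 0.51 | 0.6 | 0.85 |

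**As patients per arm.** To match ANCOVA with 27 per arm:
- a day-7 t-test needs 27/0.91 ≈ 30, 27/0.75 = 36 and 27/0.51 ≈ 53;
- a change-score t-test needs 27/0.65 ≈ 42, 27/0.75 = 36 and 27/0.85 ≈ 32.

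**As power.** Take the effect that gives the day-7 t-test 80% power: (1.96 + 0.84) × √(2/27) ≈ 0.76 SD. At that effect ANCOVA has 84%, 90% and 98% power, and the change-score t-test has 66%, 80% and 95%, for r = 0.3, 0.5 and 0.7.

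**Would imbalance-driven adjustment distort the error rate?** Null trials with 27 per arm were simulated (100,000 per setting, two arms, normal data), at a nominal 5%:

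| Rule | r = 0.3 | r = 0.5 | r = 0.7 |
|---|---|---|---|
| Adjust only if baseline p < 0.05 | 4.7% | 4.3% | 3.6% |
| Adjust only if baseline p < 0.20 | 4.5% | 3.8% | 2.6% |
| Report the better of adjusted and unadjusted | about 6.3% | about 7.3% | about 8.3% |

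Conditional adjustment is conservative. Inflation needs selective reporting, which the article does not plan.

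**The case against.** Several stronger readings are tempting, and the text does not support them.

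- **Imbalance as a trigger.** The models are to be performed without any stated condition, and no imbalance test or threshold appears. Unequal distribution may be only their purpose. This objection stands against calling it a trigger; it does not make imbalance a good rationale.
- **Tertiary outcomes resting on t-tests alone.** Linear models are provided for interval-scaled outcomes, and the diary and IPSS are among the listed baseline variables. The ANCOVA proposed here is therefore compatible with the plan, though not committed to.
- **Within-arm inference that would measure the surgery.** The IPSS outcome is worded as baseline against day 7 in each arm, and all patients undergo prostate resection. But the t-tests compare groups, no paired test is planned, and surgery common to all arms does not bias a between-arm contrast.
- **An odds ratio read against the 0.35 margin, or a logistic model that fails.** At a 95% antibiotic success rate, that arm would expect 27 × 0.05 = 1.35 failures, with a 0.95^27 ≈ 25% chance of none. But the primary hypotheses are assigned to unadjusted tests, and nothing applies a logistic odds ratio to the margin. This bears only on a supplementary model, in which the phage-placebo contrast would remain estimable.
- **A missing covariate list.** That may sit in an analysis plan that is not shown, and its absence is no finding.

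It is also fair to say that the gain may be small. Surgery falls between the two measurements, so r could be low; at r = 0.3 the saving against a day-7 t-test is only 9%. ANCOVA also spends a degree of freedom, so the realised gain is slightly below these large-sample ratios.

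**Conclusion.** The point holds in a limited form. The stated reason for adjustment is the wrong one for a randomised trial, and the plan does not commit to using baseline values it already collects for the tertiary outcomes. For assumed correlations of 0.3 to 0.7, adjusting for baseline removes 9% to 49% of the variance of a day-7 t-test and 35% to 15% of that of a change-score t-test. The comparison with change also assumes equal standard deviations at the two times; the comparison with day-7 values does not.

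A reader might infer inflated false-positive rates or a compromised primary analysis. Neither follows: adjusting only on imbalance is conservative under the null, and the primary test and the sample size do not depend on these models.

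**What to change.** For each interval-scaled tertiary outcome, make the leading analysis a between-arm linear model of the day-7 value, with treatment arm and that outcome's baseline value as terms, fitted whatever imbalance is observed. Present any t-test as supporting. Under Multivariate analysis, replace the imbalance rationale with adjustment for covariates fixed in advance on prognostic grounds.

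The cost is a few sentences in the protocol or analysis plan and slightly more analysis work. No new data, visits or patients are needed.

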## Discussion

UTIs are among the most prevalent microbial diseases and their financial burden on society is substantial. The continuing increase of antibiotic resistance worldwide is alarming; thus, well-tolerated, highly effective therapeutic alternatives are urgently needed. Although there is evidence indicating that bacteriophage therapy may be effective and safe for treating UTIs, the number of investigated patients is low and there is a lack of randomized controlled trials. Thus, well-designed prospective studies are urgently needed to draw definitive conclusions in the ambitious research field of UTIs. We therefore designed this first randomized, placebo-controlled, double-blind clinical trial to assess the efficacy and safety of intravesical bacteriophage for treating UTIs. This trial will significantly influence the future management of UTIs and form a basis for further studies involving bacteriophages for treating different bacterial infections. Moreover, the findings of our research project will provide further stimuli for competent authorities and physicians to use bacteriophages, as additional tools, in the prevention and treatment of otherwise virtually untreatable infections. In addition, the trial is multidisciplinary and will significantly influence all involved disciplines, i.e. urology, microbiology and infectious diseases. It will promote future multidisciplinary, multicenter approaches and collaborations further improving patients’ medical care and it will also raise the acceptance to use bacteriophages in western civilizations and accelerate regulations processes.

## Abbreviations

CTCAE: Common Terminology Criteria for Adverse Events
EIBMV: Eliava Institute of Bacteriophages, Microbiology, and Virology
IPSS: International Prostate Symptom Score
TNCU: Tzulukidze National Center of Urology
UTI: Urinary tract infections
